### 2.2 Secondary

1. Peripheral maternal parasitaemia at delivery (microscopic and submicroscopic)
2. Prevalence of *P. falciparum* parasitaemia in cord blood (microscopic and submicroscopic)
3. Prevalence of placental *P. falciparum* infection (histology or blood smear, microscopy and submicroscopic)
4. Mean maternal haemoglobin (g/dL) at delivery
5. Prevalence of maternal anaemia at delivery (< 11g Hb/dL)
6. Prevalence of severe maternal anaemia at delivery (< 7g Hb/dL)
7. Prevalence of neonatal anemia (Hb<12.5 g/dL in case of cord blood, or Hb <13 g/dL in case of peripheral blood )
8. Mean birth weight (in grams)
9. Prevalence of prematurity
10. Number of stillbirths
11. Number of miscarriages
12. Frequency of congenital malformations.
13. Mean gestational age at birth (assessed by Ballard score in the newborn)
14. Incidence of vomiting
15. Incidence of dizziness
16. Frequency of drug adverse reactions
17. Incidence of clinical malaria during pregnancy
18. Incidence of overall maternal admissions/outpatient attendances
19. Neonatal and infant mortality rate

---

Only in a subsample of participants

20. Incidence of clinical malaria in the first year of life
21. Peripheral maternal parasitaemia 1 month after end of pregnancy (microscopic and submicroscopic)

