## 3 Study design overview

This is a randomized open-label superiority 3 arms trial to compare 2-dose MQ with two dose of SP as IPTp in the prevention of the adverse effects of malaria during pregnancy and to compare MQ tolerability of 2 different MQ administration regimens. The three arms of the study are:

1. IPTp with SP (SP)
2. IPTp with MQ given as full dose (MQf)
3. IPTp with MQ given as an split dose (MQs)

The table 1 shows the visits and procedures schedules to the mother and the table 2 shows the visits and procedures schedule to the child.

---

At visit 4, approximately one month after end of pregnancy

Table 1: Maternal visits and procedures schedule

| Study Procedures                                    | Visit 1
Enrollment | Visit 2 | Visit 3
Delivery | Visit 4
1 Month | Unscheduled
visits | Household
visits |
|-----------------------------------------------------|-----------------------|---------|---------------------|--------------------|-----------------------|---------------------|
| Inclusion/Exclusion criteria                        | X                     |         |                     |                    |                       |                     |
| Written informed consent                            | X                     |         |                     |                    |                       |                     |
| Demographics/Medical history                        | X                     |         |                     |                    |                       |                     |
| Record of concomitant medication/
Adverse events | X                     | X       | X                   | X                  | X                     |                     |
| Physical examination / Clinical                     | X                     |         |                     |                    | X                     |                     |
| Gestational Age                                     | X                     | X       | X                   |                    | X                     |                     |
| Temperature                                         |                       |         |                     | X                  | X                     |                     |
| Blood Pressure                                      |                       |         | X                   |                    | X                     |                     |

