For the ITT analysis of primary endpoint, which includes all women recruited in the study, missing values for low birth weight will be imputed as follow: For those women with miscarriage, the event will be considered as failure and they will be assigned as having LBW. For those lost to follow-up or withdraw before delivery a sensitivity analysis of worse case scenario assuming all lost of follow-up and withdrawn women having a LBW, best case scenario assuming that none have LBW and worst case scenario assuming as LBW all missing values, will be presented. In case there were countries without malaria events, a sensitivity analysis not including those countries will be also presented.

The assumption that  $MQ_s$  and  $MQ_f$  have a similar effect on the LBW will be explored by inspection of the 90% confidence intervals of the comparison between  $MQ_s$  vs  $MQ_f$  in the ATP population. If the assumption of both MQ groups are similar is rejected, then comparison between  $MQ_s$  vs SP and  $MQ_f$  vs SP will be presented instead.

For the primary outcome, the weight of children born taken after delivery but before the seven days of life are transformed according to the method proposed by ... *Greenwod* (*to be completed*) to include in

A regression analysis of the weight and day after delivery

the analysis as if they were taken at birth. Maternal and new born haemoglobines from visit 3(Delivery) not taken in the date of the delivery will not be included in the analysis of these outcomes.

The gestational age will be based on the Ballard score, but in case of missing, it will be based on the gestational age calculated with the fundal height at recruitment.

For the frequency of vomiting, dizziness, prematurity, the proportion of women with those outcomes will be compared using the methods described for proportions before.

For the tolerability, only those vomiting and dizziness judged by the investigators to be related to the medication will be included in the analysis except vomiting during the first 60 minutes after a dose of IPTp that will always be considered related to medication.

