## 6.5 Tolerability (Safety, ITT)

Table 21: Tolerability

| Variable                            | MQ s
(N= XXX)
n      %      (95% CI) |        |                | MQ f
(N= XXX)
n      %      (95% CI) |        |                | SP
(N= XXX)
n      %      (95% CI) |        |                |
|-------------------------------------|-------------------------------------------------------|--------|----------------|-------------------------------------------------------|--------|----------------|------------------------------------------|--------|----------------|
|                                     |                                                       |        |                |                                                       |        |                |                                          |        |                |
| Any vomiting after dose 1 or 2      | #                                                     | ##.##% | (####%; ####%) | #                                                     | ##.##% | (####%; ####%) | #                                        | ##.##% | (####%; ####%) |
| Dizziness after dose 1 or 2         | #                                                     | ##.##% | (####%; ####%) | #                                                     | ##.##% | (####%; ####%) | #                                        | ##.##% | (####%; ####%) |
| At least one vomiting after dose 1  | #                                                     | ##.##% | (####%; ####%) | #                                                     | ##.##% | (####%; ####%) | #                                        | ##.##% | (####%; ####%) |
| Vomiting twice or more after dose 1 | #                                                     | ##.##% | (####%; ####%) | #                                                     | ##.##% | (####%; ####%) | #                                        | ##.##% | (####%; ####%) |
| Dizziness after dose 1              | #                                                     | ##.##% | (####%; ####%) | #                                                     | ##.##% | (####%; ####%) | #                                        | ##.##% | (####%; ####%) |

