| At least one vomiting after dose 2  | #                                                     | ##.##% | (####%; ####%) | #                                                     | ##.##% | (####%; ####%) | #                                        | ##.##% | (####%; ####%) |
| Vomiting twice or more after dose 2 | #                                                     | ##.##% | (####%; ####%) | #                                                     | ##.##% | (####%; ####%) | #                                        | ##.##% | (####%; ####%) |
| Dizziness after dose 2              | #                                                     | ##.##% | (####%; ####%) | #                                                     | ##.##% | (####%; ####%) | #                                        | ##.##% | (####%; ####%) |

N= Number of subjects in the group. n= Number of subjects with at least one symptom. CI= Confidence Interval.

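### In an open-label trial, all dizziness and all vomiting after 60 minutes enter the tolerability analysis only if the investigator calls them drug-related, so attribution alone can create or mask an arm difference

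*SAP*

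**What the plan says.** SAP section 3 describes the design: "This is a randomized open-label superiority 3 arms trial". One of its stated purposes is "to compare MQ tolerability of 2 different MQ administration regimens".

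Section 5 sets the rule for which events count. For tolerability, "only those vomiting and dizziness judged by the investigators to be related to the medication will be included in the analysis". The rule has a single exemption, for early vomiting: an episode in the first hour after a dose counts as drug-related without any judgement. Dizziness has no such automatic rule. The sentence just before the filter says that the proportions of women with vomiting and with dizziness will be compared by the methods for proportions (Fisher's exact test and a risk ratio), and it does not mention relatedness.

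Section 2.2 lists endpoint 14 as "Incidence of vomiting" and endpoint 15 as the same for dizziness, both without restriction. Endpoint 16 is separate: "Frequency of drug adverse reactions". Table 20 is titled for medication-related adverse events.

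Table 21 (section 6.5) has rows such as "Any vomiting after dose 1 or 2", plus dizziness rows, again with no mention of relatedness. Table 19 (section 6.4) shows adverse events of any cause by frequency, per arm with 95% intervals.

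**The concern.** Randomisation makes the arms comparable for all vomiting and all dizziness. It does not do so for a subset chosen after allocation by someone who knows the allocation. If an assessor is readier to blame one drug or regimen, the filtered rates differ even when the women's experience does not. If the readiness runs the other way, a real difference can disappear. Both contrasts are exposed: MQ against SP, and split against full dose, which is the stated tolerability question.

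There is also a problem of reading. Someone looking at Table 21 would take its rows as counts of all vomiting and all dizziness, whereas under section 5 they are filtered counts.

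**Working it through.** The SAP states no event rate, attribution rate or sample size for tolerability, so there is no figure of its own to reproduce. The inputs below are assumptions: two-sided 5% level, equal arms of 300 to 1,500 women, and true risk *q* of 10% to 30%, the same in both arms. The attribution probabilities *a*₁ and *a*₂ (the chance that an event is labelled related in each arm) are also assumed.

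**Dizziness.** Filtered rates are *q·a*₁ and *q·a*₂, so the expected RR = *a*₁/*a*₂, whatever *q* is.
- 80% vs 70%: 0.80/0.70 = 1.14
- 80% vs 60%: 0.80/0.60 = 1.33
- 90% vs 60%: 0.90/0.60 = 1.50

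Chance of a false p<0.05 with Fisher's exact test (4,000 simulated trials each, Monte Carlo error about 0.8 percentage point):

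| Attribution | *q* | Women per arm | False p<0.05 |
|---|---|---|---|
| 80% vs 60% | 20% | 300 | about 25% |
| 80% vs 60% | 20% | 500 | about 42% |
| 80% vs 60% | 20% | 1,000 | about 70% |
| 80% vs 60% | 20% | 1,500 | about 87% |
| 80% vs 60% | 10% | 1,000 | about 39% |
| 80% vs 60% | 30% | 1,000 | about 90% |
| 80% vs 70% | 20% | 1,000 | about 23% |

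**Vomiting.** Let *e* be the share occurring within 60 minutes, which counts without judgement. Then RR = [*e* + (1−*e*)*a*₁] / [*e* + (1−*e*)*a*₂]. With 80% vs 60%, *q* = 20% and 1,000 per arm:

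| *e* | RR | False p<0.05 |
|---|---|---|
| 0 | 0.80/0.60 = 1.33 | about 70 to 72% |
| 25% | 0.85/0.70 = 1.21 | about 42% |
| 50% | 0.90/0.80 = 1.12 | about 20% |
| 75% | 0.95/0.90 = 1.06 | about 8% |
| 100% | 1.00 | about 5% |

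**Masking.** If the true split/full RR is 0.75 and attribution is 80% on split and 60% on full, the reported RR for dizziness is 0.75 × 0.80/0.60 = 1.00.

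**Counting all events.** Attribution drops out. With equal true risks the expected RR is 1.00, and the simulated rejection rate is about 3 to 5%.

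**The case against.** The best case for the plan has five parts.

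1. *The filter is not total.* A reader of the first half of the sentence might infer that nothing counts without an investigator's opinion. That is not so. Early vomiting is always counted, and if most vomiting is early, little bias remains for that endpoint. This stands for vomiting but gives no protection for dizziness.

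2. *Endpoints 14 and 15 may be untouched.* A reader might infer a flat contradiction between the filter and these endpoints. The text does not go that far. The preceding sentence compares vomiting and dizziness without restriction, and the filter then opens as a rule for tolerability. The fair description is ambiguity: section 6 provides no separate table for the unrestricted comparison, and the only table naming these symptoms is the one the filter appears to govern.

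3. *All-cause events appear in Table 19.* This helps in part. That table fixes no row for vomiting or dizziness, and no between-arm comparison of its rows is specified.

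4. *The assessor may be masked, and the gap may be small.* Knowledge of the arm is inferred from the open-label design, and the protocol could provide masked review. A reader might also infer a doubling of risk or more, by supposing very different labelling on MQ and SP. Nothing in the SAP supports a particular gap, and the gap between two regimens of one drug could be smaller.

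5. *Denominators.* Table 21 has one N per arm, so rows such as "At least one vomiting after dose 2" include women who never took dose 2. A reader might infer that these rows must be restricted to dose-2 recipients. That does not follow. The undivided N keeps the randomised groups, whereas restriction conditions on what happened after randomisation and can itself flatter the worse-tolerated arm. Table 3 already gives dose counts by arm.

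**Conclusion.** The concern holds for all dizziness and for vomiting after 60 minutes. As written, the rule lets differential attribution create or hide a tolerability difference between split and full dose or between MQ and SP. Its direction and size cannot be derived from the document. An assumed 80% vs 60% attribution gives a spurious dizziness RR of 1.33, and a vomiting RR between 1.33 and 1.00 depending on the early share. The conclusion rests on causality being judged with the arm known, which the open-label design suggests and nothing in this SAP rules out. The mismatch between the filter and the unrestricted wording of section 2.2, section 5 and Table 21 needs no such assumption. It should be corrected, since the remedy is cheap.

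**What to change.** In section 5, define the main tolerability analysis as all vomiting and all dizziness found in the post-dose tolerability assessment, whatever the judged cause, and state the window used. Make this the main content of Table 21. Add risk ratios for split vs full and for MQ vs SP, because the shell now shows only per-arm percentages and intervals. The randomised comparison is the row for either dose; per-dose denominators may be added for description only. Report related-only events, with the 60-minute rule, as a supportive analysis labelled as such, and word the Table 21 rows so that the two versions cannot be confused.

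The cost is SAP wording and extra table rows and columns. Table 19 separates adverse events of any cause from related ones, which indicates that unrelated events are recorded. The downside is that background pregnancy vomiting and dizziness enter every arm and pull the ratio toward 1, by an amount the document does not allow to be estimated. The supportive analysis lets a reader see that effect.

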## 6 Skeleton of tables and graphs

### 6.1 Trial profile (ATP, ITT, Safety)

Table 3: Trial profile

|                                       | Screened | #               |                 |    |
|---------------------------------------|----------|-----------------|-----------------|----|
|                                       | Group    | MQ s | MQ f | SP |
| Randomized                            |          | #               | #               | #  |
| Receives ITN                          |          | #               | #               | #  |
| Withdrawn before dose 1               |          | #               | #               | #  |
| Dose 1 IPTp                           |          | #               | #               | #  |
| Withdrawn before dose 2               |          | #               | #               | #  |
| Dose 2 IPTp                           |          | #               | #               | #  |
| Withdrawn before delivery             |          | #               | #               | #  |
| Delivery                              |          | #               | #               | #  |
| Withdrawn before completing follow-up |          | #               | #               | #  |
| Visit after delivery                  |          | #               | #               | #  |

Table 4: Reasons for withdrawn before dose 1

|                                             | MQ s | MQ f | SP |
|---------------------------------------------|-----------------|-----------------|----|
| Serious Adverse Events                      | #               | #               | #  |
| Non Serious Adverse Events                  | #               | #               | #  |
| Protocol Violation - No compliance with ATP | #               | #               | #  |
| Consent withdrawal                          | #               | #               | #  |
| Migrated/moved from study area              | #               | #               | #  |
| Lost to follow-up                           | #               | #               | #  |
| End of pregnancy / Miscarriage              | #               | #               | #  |
| Others                                      | #               | #               | #  |

Table 5: Reasons for withdrawn before dose 2

|                                             | MQ s | MQ f | SP |
|---------------------------------------------|-----------------|-----------------|----|
| Serious Adverse Events                      | #               | #               | #  |
| Non Serious Adverse Events                  | #               | #               | #  |
| Protocol Violation - No compliance with ATP | #               | #               | #  |
| Consent withdrawal                          | #               | #               | #  |
| Migrated/moved from study area              | #               | #               | #  |
| Lost to follow-up                           | #               | #               | #  |
| End of pregnancy / Miscarriage              | #               | #               | #  |
| Others                                      | #               | #               | #  |

Table 6: Reasons for withdrawn before delivery

|                                             | MQ s | MQ f | SP |
|---------------------------------------------|-----------------|-----------------|----|
| Serious Adverse Events                      | #               | #               | #  |
| Non Serious Adverse Events                  | #               | #               | #  |
| Protocol Violation - No compliance with ATP | #               | #               | #  |
| Consent withdrawal                          | #               | #               | #  |
| Migrated/moved from study area              | #               | #               | #  |
| Lost to follow-up                           | #               | #               | #  |
| Others                                      | #               | #               | #  |

Table 7: Reasons for withdrawn before completing follow-up

|                                             | MQ s | MQ f | SP |
|---------------------------------------------|-----------------|-----------------|----|
| Serious Adverse Events                      | #               | #               | #  |
| Non Serious Adverse Events                  | #               | #               | #  |
| Protocol Violation - No compliance with ATP | #               | #               | #  |
| Consent withdrawal                          | #               | #               | #  |
| Migrated/moved from study area              | #               | #               | #  |
| Lost to follow-up                           | #               | #               | #  |
| Others                                      | #               | #               | #  |

## 6.2 Baseline characteristics (ATP, ITT, Safety)

Table 8: Baseline characteristics

| Variable                                            |                                    | MQ s
(N=XXX) | MQ f
(N=XXX) | SP
(N=XXX) |
|-----------------------------------------------------|------------------------------------|----------------------------|----------------------------|---------------|
| Country (n(%))                                      | Benin                              | ##.##%                     | ##.##%                     | ##.##%        |
|                                                     | Gabon                              | ##.##%                     | ##.##%                     | ##.##%        |
|                                                     | Mozambique                         | ##.##%                     | ##.##%                     | ##.##%        |
|                                                     | Tanzania                           | ##.##%                     | ##.##%                     | ##.##%        |
| Age (years, mean(sd))                               |                                    | ##.##                      | ##.##                      | ##.##         |
| Gravity (n(%))                                      | Primigravidae                      | ##.##%                     | ##.##%                     | ##.##%        |
|                                                     | 1 to 3 previous pregnancies        | ##.##%                     | ##.##%                     | ##.##%        |
|                                                     | 4 or more                          | ##.##%                     | ##.##%                     | ##.##%        |
| Weight (kg, mean(sd))                               |                                    | ##.##                      | ##.##                      | ##.##         |
| Height (cm, mean(sd))                               |                                    | ##.##                      | ##.##                      | ##.##         |
| MUAC (cm, mean(sd))                                 |                                    | ##.##                      | ##.##                      | ##.##         |
| Gestational age at recruitment (weeks, median(IQR)) |                                    | ##.##                      | ##.##                      | ##.##         |
| Gestational age in categories                       | First trimester (0-12 weeks)       | ##.##%                     | ##.##%                     | ##.##%        |
|                                                     | Second trimester (12-24 weeks)     | ##.##%                     | ##.##%                     | ##.##%        |
|                                                     | Third trimester ( $\geq 25$ weeks) | ##.##%                     | ##.##%                     | ##.##%        |
| Literate (can read and/or write, n(%))              |                                    | ##.##%                     | ##.##%                     | ##.##%        |
| Syphilis test (Positive, n(%))                      |                                    | ##.##%                     | ##.##%                     | ##.##%        |
| Hemoglobin (g/dl, mean(sd))                         |                                    | ##.##                      | ##.##                      | ##.##         |
| Anaemia (Hb < 11, n(%))                             |                                    | ##.##%                     | ##.##%                     | ##.##%        |
| Severe anaemia (Hb < 7, n(%))                       |                                    | ##.##%                     | ##.##%                     | ##.##%        |

N: Number of subjects in the group, sd: Standard deviation, n: Number of subjects in the category IQR: Interquartile range, %: Percentage

